## Abstract

**Introduction:**

Bronchiectasis is a worldwide chronic lung disorder where exacerbations are common. It affects people of all ages, but especially Indigenous populations in high-income nations. Despite being a major contributor to chronic lung disease, there are no licensed therapies for bronchiectasis and there remain relatively few randomised controlled trials (RCTs) conducted in children and adults. Our RCT will address some of these unmet needs by evaluating whether the novel mucoactive agent, erdosteine, has a therapeutic role in children and adults with bronchiectasis.

Our primary aim is to determine in children and adults aged 2–49 years with bronchiectasis whether regular erdosteine over a 12-month period reduces acute respiratory exacerbations compared with placebo. Our primary hypothesis is that people with bronchiectasis who regularly use erdosteine will have fewer exacerbations than those receiving placebo.

Our secondary aims are to determine the effect of the trial medications on quality of life (QoL) and other clinical outcomes (exacerbation duration, time-to-next exacerbation, hospitalisations, lung function, adverse events). We will also assess the cost-effectiveness of the intervention.

**Methods and analysis:**

We are undertaking an international multicentre, double-blind, placebo-RCT to evaluate whether 12 months of erdosteine is beneficial for children and adults with bronchiectasis. We will recruit 194 children and adults with bronchiectasis to a parallel, superiority RCT at eight sites across Australia, Malaysia and Philippines. Our primary endpoint is the rate of exacerbations over 12 months. Our main secondary outcomes are QoL, exacerbation duration, time-to-next exacerbation, hospitalisations and lung function.

**Ethics and dissemination:**

The Human Research Ethics Committees (HREC) of Children’s Health Queensland (for all Australian sites), University of Malaya Medical Centre (Malaysia) and St. Luke’s Medical Centre (Philippines) approved the study. We will publish the results and share the outcomes with the academic and medical community, funding and relevant patient organisations.

**Trial registration number:**

ACTRN12621000315819.

WHAT IS ALREADY KNOWN ON THIS TOPICBronchiectasis, ranking only behind asthma and chronic obstructive pulmonary disease as the most common chronic pulmonary disorder globally, is under-researched especially in children, with large knowledge gaps and no licensed therapies. Erdosteine, a novel oral mucoactive agent possessing additional anti-inflammatory and anti-microbial properties, may provide a clinical benefit.WHAT THIS STUDY ADDSThis is the first randomised controlled trial to combine children and adults with bronchiectasis into a single trial. It is also the first trial of erdosteine in people with bronchiectasis to inform whether this novel agent is well tolerated and reduces acute exacerbations and improves quality of life in this group of patients.HOW THIS STUDY MIGHT AFFECT RESEARCH, PRACTICE OR POLICYIf a clinical benefit is demonstrated, erdosteine could be easily incorporated into routine clinical practice, especially if well tolerated and cost-effective.

## Introduction

Bronchiectasis unrelated to cystic fibrosis (CF) is a chronic lung disorder affecting all age groups.^1^ It is characterised clinically by recurrent or persistent wet/productive cough, lower airway infection and inflammation, and radiographically by abnormal bronchial dilatation seen on chest CT scans.^1 2^ Acute exacerbations identified by new or worsening respiratory symptoms are also common and are important contributors to the overall burden of disease.^3^

The high prevalence of bronchiectasis among Indigenous children in high-income countries is well known. In remote Australian Indigenous communities of Central and Western Australia, bronchiectasis rates in children have remained stubbornly high at 1.5% during the last 20 years.^4 5^ In contrast, its burden among Indigenous children living in low-income and middle-income countries^6^ and non-Indigenous children is underappreciated,^7 8^ despite bronchiectasis ranking only behind asthma and chronic obstructive pulmonary disease (COPD) as the most common chronic pulmonary disorder worldwide^9^ resulting in substantial morbidity and mortality.^1 7^ Deemed by the European Respiratory Society (ERS) as one of the most neglected lung diseases in clinical practice,^10^ bronchiectasis, especially in children, is relatively under-researched^11^ and underserviced^12^ with large unmet needs.^13–15^ Consequently, critical, clinically relevant gaps remain,^13–15^ including the absence of licensed therapies for bronchiectasis and scarce data on acute respiratory exacerbations.^1^

Current guidelines^2 16 17^ for managing children and adults with bronchiectasis depict the limited availability of therapies specific to bronchiectasis. General therapies include nutritional care, additional vaccinations and pulmonary rehabilitation in adults while specific therapies comprise airway clearance techniques, antibiotics (for managing and preventing acute exacerbations^18 19^) and mucoactive agents (eg, hypertonic saline and mannitol). Without licensed therapies and high-level evidence, many current interventions used in people with bronchiectasis are generally extrapolated from studies and clinical experience gained from treating people with CF.^7^ However, given the very different pathobiological mechanisms between bronchiectasis and CF, it is of no surprise that some selected therapies, which are beneficial for CF, can be deleterious for people with bronchiectasis (eg, dornase alfa).^7^

The pathobiology of bronchiectasis includes the coexistence of chronic lower airway infection and inflammation, mucus hypersecretion and disruption of mucociliary clearance, which are all integral to the vicious vortex (previously labelled the vicious cycle) hypothesis of bronchiectasis,^7 20^ and are also thought to operate in people with COPD.^21^ Clinically these processes result in wet/productive cough, symptoms that are particularly bothersome for people with bronchiectasis.^14^

Recurrent respiratory exacerbations are also a characteristic feature of broncheictasis.^20 22^ Reducing exacerbations is important as these episodes impair quality of life (QoL) and can lead to an accelerated decline in lung function and high utilisation of healthcare resources.^20 22–24^ A prospective multicentre study involving 85 children with bronchiectasis found that the mean number of exacerbations was 3.3 (SD 2.2) per child-year.^25^ In any given month, 25% of these children were absent from school/childcare, 30% attended a healthcare appointment and 46% received antibiotics due to bronchiectasis while 11.4% of respiratory exacerbations required hospitalisation.^25^

Interventions that might reduce respiratory exacerbations and sputum volume would be beneficial to people with bronchiectasis as these factors are considered by clinicians and patients as the most challenging aspects of managing bronchiectasis.^13 14^ Mucoactive agents, such as erdosteine, are one such intervention that could address both of these patient and clinician priorities.^26–28^

Erdosteine is a novel thiol derivative, synthesised to overcome problems (eg, non-efficacy and toxicity related to increased free thiols in the circulation) observed with other thiols (eg, N-acetylcysteine).^21^ It is licensed currently in 40 countries, including the UK (it has orphan drug status in the USA,^29^ but not in Australia.^29^ Erdosteine is administered orally and has four main properties that could moderate the effects of ciliary dysfunction in the lungs (and thus potentially reduce exacerbations and improve QoL in people with bronchiectasis. These are as follows: (1) a mucoactive agent, modulating mucus production and viscosity, and increasing mucociliary transport; (2) an antioxidant; (3) airway anti-inflammatory and (4) bacterial antiadherence properties.^21 30^ Erdosteine has been used for short-term studies of acute respiratory infections in children (aged >1 year)^31^ and shown to be safe in these studies, which collectively involved approximately 500 children.^31–33^

The syndrome of chronic bronchitis (ie, chronic productive cough) is a component of bronchiectasis; in both conditions, mucus hypersecretion and dysfunctional mucociliary clearance are present.^1 34^ In a meta-analysis of 10 randomised controlled trials (RCTs), erdosteine (vs placebo) improved the clinical outcomes of adults with either COPD or chronic bronchitis (ie, improved global overall clinical scores, reduced exacerbations by 35% and hospitalisation by 44%).^35^ A short-term small (n=30) RCT in adults with radiographic bronchiectasis also found improved clinical outcomes (better cough and dyspnoea scores, 6 min walk test) on day 15.^36^ However, as with long-term macrolides to reduce acute exacerbations,^1 7^ such medications are usually given for prolonged periods and this 15-day study was too short to determine whether the observed clinical benefits were sustained.

The coexistence or overlap of COPD with bronchiectasis has long been recognised. A meta-analysis of 18 studies found that the prevalence of bronchiectasis in COPD was 54% (range 25%–69%).^37^ Another meta-analysis of 14 observational studies described comorbid bronchiectasis in COPD with increased the risk of exacerbation (1.97, 95% CI 1.29 to 3.00), severe airway obstruction (1.31, 95% CI 1.09 to 1.58) and mortality (1.96, 95% CI 1.04 to 3.70).^38^ This meta-analysis also reported a wide range of coexistent bronchiectasis from 4% to 72%.^38^ Consequently, studies involving erdosteine in adults with COPD are also relevant in informing the rationale for our study.

In adults with COPD, a systematic review of interventions for preventing respiratory exacerbations included two RCTs using erdosteine.^27^ Both RCTs (8–12 months duration) found that erdosteine significantly reduced hospitalisation, antibiotic use and respiratory exacerbations and improved QoL and lung function.^27^ A meta-analysis^28^ of individual patient data (n=1046) on erdosteine also found it was associated with significant symptom amelioration, compared with either placebo or other mucoactive agents in patients with chronic bronchitis/COPD. A network meta-analysis^39^ (seven RCTs) found that erdosteine was superior to other mucoactive agents (eg, carbocysteine) for reducing acute COPD respiratory exacerbations and hospitalisation. A more recent post hoc RCT analysis of adults with moderate-to-severe COPD also described clinical benefits when erdosteine was added to their usual maintenance therapy for a 12-month period (compared with placebo).^40^ The improved clinical outcomes included improved QoL and patient-reported disease severity and reduction in proportion of patients who had exacerbations requiring antibiotics and/or corticosteroids (74.3% vs 80.8%, p<0.05).^40^

Thus, erdosteine is a promising novel mucoactive that may be beneficial for people with bronchiectasis. It is possible, but unknown, if prolonged treatment for 12 months will benefit children and young adults with bronchiectasis. As these actions target part of the underlying pathobiological mechanisms in people with bronchiectasis, it is plausible that regular erdosteine could improve clinical outcomes.

### Aims and hypotheses

Our primary aim is to determine in children and adults aged 2–49 years with bronchiectasis whether regular erdosteine over a 12-month period reduces acute respiratory exacerbations compared with placebo. Our primary hypothesis is that people with bronchiectasis who regularly use erdosteine will have fewer exacerbations than those receiving placebo.

Our secondary aims are to determine the effect of the trial medications on QoL and other clinical outcomes (exacerbation duration, time-to-next exacerbation, hospitalisations, lung function, adverse events). Our secondary hypotheses are that regular erdosteine improves QoL and other clinical outcomes.

Additionally, we will also the assess cost-effectiveness of the intervention by collecting healthcare-related costs and calculate the incremental cost-effectiveness ratio of the active treatment. Our additional hypothesis is that regular erdosteine will be associated with less exacerbation-related healthcare resource utilisation and costs. Finally, there is a discovery aim to determine if blood gene expression and/or microbial biomarkers will identify pathways and/or predict those at greater risk of recurrent respiratory exacerbations.

## Methods and analysis

### Design

We are undertaking a parallel, double-blind, placebo, superiority multicentre RCT (with concealed allocation) to determine the efficacy of 12 months of erdosteine at reducing acute respiratory exacerbations and improving other clinical outcomes. We randomised the first participant in May 2021 and we anticipate continuing recruitment until at least July 2024. This RCT started recruiting concurrently with our other RCT that also involved erdosteine in one of its arms, where the goal was to reduce exacerbations in people with primary ciliary dyskinesia.^41^ Thus, these RCTs have many shared methods and descriptions of data collected.

### Study settings and participants

#### Study sites

Our current study sites are across three countries: Australia, Malaysia and the Philippines. The Australian sites are Queensland Children’s Hospital (Brisbane), Mater Hospital (Brisbane), Concord Repatriation Hospital (Sydney), Perth Children’s Hospital (Perth), Royal Darwin Hospital (Darwin) and Gold Coast University Hospital (Gold Coast). The Malaysian site is the University of Malaya Medical Centre (Kuala Lumpur) and in the Philippines, children are recruited from St Luke’s Hospital (Quezon City). Adults are recruited only from the Mater and Concord Repatriation Hospitals.

#### Inclusion criteria

Inclusion criteria are as follows: (1) Children or adults aged 2–49 years, (2) have radiographic-confirmed bronchiectasis with at least two exacerbations or one hospitalisation for an acute respiratory exacerbation in the last 18 months and (3) are able to be contacted for the 15-month follow-up period.

#### Exclusion criteria

Exclusion criteria are as follows: (1) CF, (2) contraindications for erdosteine (eg, liver dysfunction, hypersensitivity, renal failure, cystathionine-synthetase enzyme deficiency, phenylketonuria, active peptic ulcer disease), (3) pregnant, pregnancy planned (in the next 12 months) or nursing mothers, (4) previously randomised, (5) hospitalised in the last 4 weeks for a respiratory illness, (6) if another household member is a participant in this study or (7) active participation in another RCT.

#### Recruitment

Potential participants are identified from clinic lists and hospital databases and are approached by a research team member uninvolved in their clinical care. Those fulfilling the eligibility criteria and are willing to participate will have the study explained to them by a member of the research team using an information booklet, as well as providing consent documents and interpreters (where appropriate). After all aspects of the study are explained and agreed on, written informed or electronic consent (e-consent) is obtained from the parent/guardian/participant, including assent in children aged 12–17 years. Our processes are consistent with the principles of Good Clinical Practice (GCP), the Declaration of Helsinki and the Australian National Health and Medical Research Council (NHMRC) requirements and cultural aspects of consent for Indigenous Australians.

### Study protocol

A summary of our protocol is summarised in the figure 1. All participants are managed according to local clinical protocols for their other bronchiectasis-related care.

**Figure 1 F1:**
[figure not shown]
Overall schematic study design of our randomised controlled trial. QoL, quality of life; RE, respiratory exacerbation.

#### Trial medications

Erdosteine is available as oral powder for suspension (175 mg/5 mL) or capsules (300 mg) administered two times per day for 12 months. Doses are weight based, that is, <15 kg: 2.5 mL/dose; 15–19 kg: 5 mL/dose; 20–30 kg: 7.5 mL/dose or one capsule; >30 kg: 10 mL/dose or one capsule. Equivalent placebo capsules or oral suspension also match the active preparation. We purchased erdosteine and its corresponding placebo from the manufacturers (Recipharm, Paderno Dugnano, Italy).

#### Randomisation, allocation concealment and blinding

Randomisation is undertaken by each study site’s pharmacy using REDCap where the sequence is stratified by site in permuted blocks sizes of 4–8. Allocation is thus undertaken by the local hospital pharmacist (or representative) who then dispenses the trial medications to the participant. Trial medications are dispensed every 3 months and adherence is monitored by return of bottles, collection of study medications and parent reports.

People who are blinded to treatment allocation are (1) receiving the treatment, (2) administering the treatment, (3) assessing the outcomes and (4) analysing the results/data.

#### Data and sample collection, monitoring and follow-up details

All collected data are recorded by GCP-trained researchers using standardised data sheets or online surveys (similar to our previous RCTs).^18 19 42^

At enrolment, sociodemographic/clinical data, spirometry (in those aged >6 years) and specimens (sputum and blood where possible in a subset of participants contributing to the discovery component) are collected (table 1).

**Table 1 T1:** Schedule for visits and contact points

Visit type	Baseline	Month												
		1	2	3	4	5	6	7	8	9	10	11	12	Start of exacerbation (if possible)
Screening for eligibility	√													
Informed consent (paper or electronic)	√													
Randomisation	√													
Medical history	√													
Medical chart review	√			√			√			√			√	
Monthly parent/participant contact recording exacerbations		√	√	√	√	√	√	√	√	√	√	√	√	
Clinical assessment (where possible)	√			√			√			√			√	√
PC-QoL-and/or QoL-B questionnaire	√						√						√	√
Spirometry (if possible)	√			√			√			√			√	√
Urine pregnancy test (only females ≥14 years	√						√						√	
Study diary	√						√						√	√
Blood in subgroup	√													√
Sputum in subgroup	√													

B-QoL, bronchiectasis QoL tool; PC-QoL, Parent-proxy Cough QoL-8 instrument; QoL, quality of life.

Sociodemographic data include details of age, gender, family and household size, cigarette smoking, family and immunisation history, medications and comorbidities. These are obtained from the carers/participants and/or reviewing the medical notes. Participants are contacted every month via electronic communication (email or short-message service texting) or by telephone to monitor progress and adverse events (eg, vomiting, diarrhoea, rash) and economic data (eg, medical visits, treatments, other interventions, school/work absenteeism). Participants are seen in the clinic 3–4 monthly as part of their routine clinical care (if they reside locally at one of the study sites) and at the onset of their first exacerbation following enrolment where additional clinical data and biological specimens are collected (table 1), if possible. Specimens will be stored and analysed later. We have established robust methods for capturing respiratory exacerbations.^18 19 43^ Hospital records are also reviewed for hospitalisations. Additionally, at enrolment, a pregnancy test is undertaken if a female participant is aged ≥14 years.

Exit criteria include consent withdrawn, severe study-related adverse events, intolerance to study medications or any other clinical indication as determined by study site doctors, treating clinicians or the independent data monitoring committee (iDMC). Unblinding, if necessary, will be done by the site’s pharmacy

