### Outcomes and endpoints

Our primary outcome is the acute respiratory exacerbation rate by 12 months postrandomisation. These are collected by participant reports (active surveillance of participants) and medical records.

In children, we will use the definition used previously^18 43^ that is also in accordance with the ERS-based guidelines^2^ and the ERS Task Force international consensus definition of an exacerbation.^3^ For children, an episode is defined by an acute respiratory event that (1) is treated with antibiotics and (2) has an increase in sputum volume and/or purulence, or >3 days of change in cough (at least 20% increase in cough score or change in quality (dry to wet/productive)) or physician-confirmed acute change in respiratory rate, effort or chest signs.^3^ For adults (aged>18 years), we will use the adult consensus definition that is, a clinician determines that treatment change is required and deterioration in ≥3 of the following for ≥48 hours (cough, sputum volume or purulence, breathlessness, exercise tolerance, fatigue and/or malaise, haemoptysis).^24^

Other outcomes (see online supplemental material for further information) are as follows:

10.1136/bmjresp-2023-002216.supp1Supplementary data

QoL scores at 12 months: In adults, we are using the bronchiectasis QoL tool (B-QoL),^44^ which has 37 questions with a respiratory subdomain score. In the absence of a bronchiectasis-specific QoL for children, we are using the validated Parent-proxy Cough QoL-8 instrument (PC-QoL).^45^
Time-to-next exacerbation: Defined from the time of commencing trial medications to the next respiratory exacerbation (defined above), measured in days.Time-to-next respiratory-related hospitalisation.Spirometry values (forced expiratory volume in 1 s (FEV_1_ z-score) and forced vital capacity (FVC) z-score, and FEV_1_/FVC ratios).Adverse events, including gastrointestinal symptoms (eg, nausea, vomiting, abdominal pain, diarrhoea), headaches, rashes, use of additional non-macrolide antibiotics for non-pulmonary infections during the intervention, that is, for 12 months postrandomisation.Healthcare resource use.

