### Data monitoring, management and analyses

All identifiable information on study participants will be retained in password-protected files stored on the QUT server or locked cabinets/rooms at study sites. Access to this information will only be provided to immediate study staff unless required by legislative or regulatory agencies and the HRECs. The principal investigator and statisticians will have access to the final trial dataset.

All adverse events, including serious adverse events, are monitored by an iDMC, which was established prior to commencing the study. An Indigenous (First Nations) Reference Group based at the Menzies School of Health Research (Darwin) oversees the cultural aspects of the study. Data coding and entry are coordinated in Brisbane and conducted in accordance with GCP.

The analyses will be directed by biostatisticians ([name] and [name]). Results will be reported and presented in accordance with Consolidated Standards of Reporting Trials guidelines. We will use the ‘intention-to-treat’ approach for the main analyses. We also plan a ‘per-protocol’ analysis. Missing data will not be imputed. No interim analysis is planned. A detailed statistical analysis plan will be developed and approved by the chief investigators and the iDMC before undertaking the final analysis. Any exploratory, post hoc or unplanned analysis will be identified clearly. Analysis code will be written and agreed on knowledge of treatment allocation and adherence is provided to the statistician, as done previously.^18 43^

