#### For the primary aim

To assess erdosteine efficacy, the exacerbation rate in those randomised to receive erdosteine will be compared with controls (receiving placebo). We will use a negative binomial regression model (as recommended,^46^ including treatment group, and number of months in the study included as an offset) to determine between-group differences (with 95% CI), as done previously.^19^

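### The exit criteria do not separate stopping trial medication from leaving the study, so the 12-month intention-to-treat comparison is not secured

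*Protocol article*

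**What the plan says.** The exit rule stands in the protocol article under Data and sample collection, monitoring and follow-up details: "Exit criteria include consent withdrawn, severe study-related adverse events, intolerance to study medications or any other clinical indication". The clinical indication may be judged by site doctors, treating clinicians or the data monitoring committee. Nothing nearby describes a participant who stops medication but stays in follow-up.

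Other sections bear on how that rule works:

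- Outcomes and endpoints: "Our primary outcome is the acute respiratory exacerbation rate by 12 months postrandomisation", and on the source of the data, "These are collected by participant reports (active surveillance of participants) and medical records".
- Data monitoring, management and analyses: "We will use the ‘intention-to-treat’ approach for the main analyses", with a separate per-protocol analysis, and "Missing data will not be imputed".
- For the primary aim: a negative binomial model with the "number of months in the study included as an offset".
- Sample size: power rests on 164 people with final endpoint data, with a 25% allowance for attrition.
- Table 1: contact about exacerbations every month to month 12, and chart review at months 3, 6, 9 and 12.
- Inclusion criteria: participants must be people who "are able to be contacted for the 15-month follow-up period".

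**The concern.** Withdrawn consent normally ends data collection. Intolerance and study-related adverse events need not, yet the exit rule gives them the same status. If a participant who stops for intolerance also leaves follow-up, later exacerbations go uncollected. The offset then shortens that person's exposure time, and nothing is imputed.

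The estimate would then describe the rate while participants remained in the study, not the rate over 12 months in the groups as randomised. The two differ if benefit is lost after stopping, or if those who leave differ in exacerbation risk and the arms lose different people. Drug-related reasons make both possible. The primary result is what is at stake.

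This goes beyond analysis detail that an article may leave to the analysis plan. It is a stated conduct rule that merges two events, and an analysis plan cannot recover reports that were never taken. The child definition of an exacerbation needs antibiotic treatment plus symptom or sign criteria. The adult definition needs a clinician's decision to change treatment plus deterioration lasting at least 48 hours. Record review alone could miss events of either kind.

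**Working it through.** **Inputs from the article.** Control rate λ0 = 3 per year and erdosteine rate λ1 = 1.8 per year (Sample size), so the planned ratio is 1.8/3 = 0.60. The article gives no exit rates by arm, no exit times and no post-stopping rates, so there is no figure of its own to reproduce on this point.

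**Assumptions for the illustration.** A fraction d of the erdosteine arm exits at s = 0.25 years, nobody exits on placebo, and the rate returns to λ0 after stopping.

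*In-study ratio.* Events are (1−d)λ1 + d·s·λ1 and time is (1−d) + d·s. Their quotient is λ1 for any d, so the ratio is 1.8/3 = 0.60.

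*12-month ratio.* [(1−d)λ1 + d(sλ1 + (1−s)λ0)]/λ0. A leaver's 12-month count is 0.25×1.8 + 0.75×3 = 2.7.

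- d = 10%: (0.9×1.8 + 0.1×2.7)/3 = 1.89/3 = 0.63
- d = 25%: (0.75×1.8 + 0.25×2.7)/3 = 2.025/3 = 0.675

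**If leavers have higher underlying rates.** Suppose the people who would leave have 1.5 times the rate of those who would not, equally in both arms. Set the non-leavers' control rate to 1. For d = 10%:

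- control: 0.9 + 0.1×1.5 = 1.05
- 12 months: [0.9×0.6 + 0.15×(0.25×0.6 + 0.75)]/1.05 = 0.675/1.05 = 0.643
- in study: [(0.54 + 0.15×0.25×0.6)/(0.9 + 0.1×0.25)]/1.05 = (0.5625/0.925)/1.05 = 0.579

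The result depends on what the 1.5 multiplies:

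| Leavers' rate | Exits | In-study ratio | 12-month ratio |
|---|---|---|---|
| Same as others | 10% | 0.60 | 0.63 |
| Same as others | 25% | 0.60 | 0.675 |
| 1.5 × non-leavers' rate | 10% | 0.579 | 0.643 |
| 1.5 × non-leavers' rate | 25% | 0.554 | 0.700 |
| 1.5 × overall average | 10% | 0.576 | 0.645 |
| 1.5 × overall average | 25% | 0.531 | 0.713 |

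**Simulation of the planned model.** There were 400 runs with 97 per arm, gamma-Poisson counts, a negative binomial fit with log-time offset, and exit times averaging about 3 months. The article states no dispersion. The value used, 0.574, is the one that makes 164 people give 90% power (two-sided, 1:1, one year each). Risk-related means that the chance of exit rises with a person's own exacerbation rate.

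| On-drug ratio | Exits, erdosteine / placebo | Risk-related | In-study ratio | 12-month ratio |
|---|---|---|---|---|
| 1.00 | 25% / 5% | no | 0.995 | 0.997 |
| 1.00 | 25% / 25% | yes | 0.987 | 0.990 |
| 1.00 | 25% / 5% | yes | 0.920 | 1.003 |
| 0.60 | 15.5% / 15.5% | no | 0.605 | 0.652 |
| 0.60 | 25% / 5% | no | 0.595 | 0.673 |
| 0.60 | 25% / 5% | yes | 0.540 | 0.709 |

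The 15.5% is the loss implied by 164 of 194 (1 − 164/194).

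With no drug effect, false significant results in favour of erdosteine from the in-study analysis were 2.0%, 2.2% and 9.8% in the first three rows, against a nominal 2.5%. The Monte Carlo standard error of the 9.8% is √(0.098×0.902/400), about 1.5 percentage points.

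**What follows.** With no drug effect, bias needs exits that both differ by arm and relate to risk. With a real effect that is lost on stopping, the in-study and 12-month ratios differ even when exits are equal.

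**The case against.** A reader might infer that the plan discards every exacerbation after medication stops, and so runs an on-treatment analysis under an intention-to-treat label that favours erdosteine. The article does not support that. No sentence says that exit ends follow-up. The outcome window runs from randomisation, and Table 1 does not tie its contacts to taking medication. Contactability is required for 15 months. The offset counts months in the study, not months on drug, and a separate per-protocol analysis would lose much of its purpose if the main one already stopped at discontinuation. These points stand. They make loss of post-stopping data a possibility, not a stated fact.

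It is also fair that an offset is the usual way to handle unequal follow-up, and that the direction of any bias is not fixed. If high-rate placebo participants left more often, the in-study ratio would move against erdosteine. The 25% example is an unfavourable case: it takes an all-cause allowance for the whole trial and applies it to one arm. At 10% exits with no difference in risk, the gap is small (0.63 against 0.60).

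The last defence is that a condensed article leaves such detail to the full protocol. That would answer mere silence. Here the article states a rule that puts drug-related reasons and withdrawn consent in one category, within its account of follow-up. It also allows for varying months in the study and for attrition. The ambiguity is in what is written.

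**Conclusion.** The point holds as an unresolved ambiguity in a stated conduct rule. The exit criteria merge stopping medication with leaving the study. Together with the months-in-study offset and no imputation, this leaves the intention-to-treat comparison to 12 months unsecured.

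The size cannot be fixed from the article. Under the illustrative assumptions, a 12-month ratio of 0.63 (10% exits) or 0.675 (25% exits) would be reported as 0.60, and the gap widens if leavers have higher exacerbation rates. All of these figures rest on assumed exit rates, exit at 3 months and full loss of benefit afterwards. If participants who stop medication are in fact followed to month 12, there is no bias from this source and only the wording needs correcting. The matter deserves action because the correction is cheap and the primary result depends on it. No view is taken on when medication should be stopped.

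**What to change.** State that stopping trial medication is not exit from the study. Unless consent for follow-up is withdrawn, continue the monthly contacts, chart reviews and scheduled assessments already in Table 1 to month 12. Count all exacerbations to month 12 in the primary analysis, keep the offset for the time actually followed, and leave the on-medication comparison to the per-protocol analysis. The criteria for stopping medication stay as they are.

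If this is already practice, one clarifying sentence is enough. Otherwise it needs a short amendment and a small added contact burden for those who stop, using text, email, telephone and record review already in place.

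There are two limits. The first participant was randomised in May 2021, so data not collected from people who have already exited cannot be fully recovered. Counting all 12 months can also dilute the effect. In the same-rate illustration, with 82 per arm and the back-calculated dispersion of 0.574, power falls from 90% to 84% with 10% exits and 72% with 25%. That is the power for the comparison that the article says it will make.
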